## Abstract

**Background:**

Women with highly penetrant *BRCA* mutations have a 55–60 % lifetime risk for breast cancer and a 16–59 % lifetime risk of developing ovarian cancer. However, penetrance differs interindividually, indicating that environmental and behavioral factors may modify this risk. It is well documented that the risk for sporadic breast cancer disease can be modified by changing lifestyle factors that primarily include physical activity, dietary habits, and body weight. It can thus be hypothesized that the modification of these lifestyle factors may also influence the incidence and progression of cancer in *BRCA* mutation carriers.

**Methods/design:**

This multicenter, interdisciplinary, prospective, two-armed, randomized (1:1) controlled trial aims to enroll a minimum of 600 *BRCA1* and *BRCA2* mutation carriers to partake in either a lifestyle intervention or usual care. The study primarily aims to demonstrate an improvement of nutritional behavior (adherence to the Mediterranean diet), body mass index, and physical fitness. Furthermore, the effects on quality of life, stress coping capacity, breast cancer incidence, and mortality will be investigated. The intervention group (IG) will receive a structured lifestyle intervention over 12 months, whereas the control group (CG) will only receive information regarding a healthy lifestyle. During the first 3 months, women in the IG will receive structured, individualized, and mainly supervised endurance training with a minimum of 18 MET-h physical activity per week and nutrition education based on the Mediterranean diet. Over the following 9 months, IG monthly group training sessions and regular telephone contacts will motivate study participants. The CG will receive one general training session about healthy nutrition in accordance with the recommendations of the German Society of Nutrition (standard of care in Germany) and the benefits of regular physical activity on health status. At randomization and subsequent time points (3 and 12 months), cardiopulmonary fitness will be assessed by spiroergometry, and nutritional and psychological status will be assessed by validated questionnaires, interviews, and clinical examinations.

**Discussion:**

As data on the role of lifestyle intervention in women with a hereditary risk for breast and ovarian cancer are currently lacking, this study will be of major importance from a scientific, as well as a practical advice viewpoint. It will investigate the optimal strategy to improve physical fitness, nutritional status, and psychological factors such as quality of life, perceived stress, optimism, as well as incidence and outcome of cancer in this selected group of women at high risk. If the study indicates a positive long-term outcome, a structured lifestyle intervention program could be added to health care prevention strategies for *BRCA1* and *BRCA2* mutation carriers.

**Trial registration:**

ClinicalTrials.gov: NCT02516540. Registered on 22 July 2015.

**Electronic supplementary material:**

The online version of this article (doi:10.1186/s13063-016-1504-0) contains supplementary material, which is available to authorized users.

## Background

Women with highly penetrant *BRCA* mutations have a 55–60 % risk for breast cancer and a 16–59 % risk of developing ovarian cancer [1, 2]. However, since penetrance rates are not 100 %, it can be postulated that risk-modulating factors do exist. It can be shown that the risk of development of cancer in gene carriers may be influenced through genetic factors (polymorphisms) as well as exogenous factors such as number of pregnancies, year of birth, and physical activity during youth [3, 4]. The risk for breast cancer is lower if gene carriers were born before 1940, have given birth, or were physically active during their youth [5, 6].

The risk for developing sporadic breast cancer is considerably influenced by physical activity, nutrition, and body weight factors which also affect disease progression. Likewise, it has been demonstrated in several prospective studies that regular physical activity can significantly reduce breast cancer incidence in postmenopausal and premenopausal women, the risk being reduced on average by 25 % [7]. Furthermore, the risks of recurrence and mortality in women with breast cancer are reduced by 50 % if they engage in regular physical activity [8]. Further advantages of physical activity include a gain in the quality of life, increased fitness, and better tolerance of chemotherapy [9]. Nutrition also influences the risk for breast cancer. Obesity and weight gain increase the risk of breast cancer in both pre- and postmenopausal subjects [10]. A weight gain of more than 20 kg after the age of 18 doubles the risk for breast cancer. Furthermore, women with a body mass index (BMI) of >30 kg/m^2^ have a greater risk of developing distant metastases and of dying of breast cancer [11]. In a prospective study of patients with sporadic breast cancer who were given adjuvant standard therapy, a calorie- and fat-reduced nutrition program led to a significant improvement in recurrence rate [12]. Additionally, in the prospective PREDIMED prevention trial, women in the Mediterranean diet arm supplemented with extra-virgin olive oil had a 68 % lower risk for breast cancer compared with the controls [13].

Further risk factors for breast cancer include depression, a pessimistic outlook on life, and problems of coping with stress [14, 15]. It was shown that physical activity has a favorable influence on stress management and depression. Many studies have convincingly documented the great significance of an optimistic life perspective for different psychological and somatic disorders [16]. A positive correlation was shown between an optimistic outlook on life and psychological well-being, health, stress reduction, and mortality, as well as a quicker recovery rate [17–19].

So far, no studies exist in this context on women with hereditary breast cancer or women with a deleterious *BRCA* mutation. Even retrospective data are rare. There is only one publication on this subject by Manders in 2011 [20], which reports on an association between increased body weight and an increased risk for breast cancer in *BRCA1/2* mutation carriers.

We therefore aim to examine whether a lifestyle intervention in the form of structured physical endurance training and nutrition education, emphasizing the Mediterranean dietary pattern, will lead to an improvement of nutritional behavior (adherence to the Mediterranean diet), BMI, physical fitness, quality of life, and optimistic outlook on life, and cause a significant reduction of the perceived stress. Secondary aims of the study are to investigate whether the intervention will lead to a reduction of breast cancer incidence and breast cancer mortality in *BRCA1* and *BRCA2* mutation carriers.

## Design/methods

### Trial design

The study is a multicenter, prospective, two-armed randomized (1:1) controlled clinical trial. The primary aim of the study is to evaluate whether a structured, one-year exercise program combined with a Mediterranean dietary pattern in *BRCA* mutation carriers will improve BMI, physical fitness (ventilatory threshold VT1 in spiroergometry), and adherence to a Mediterranean diet in the intervention group. Additionally, we will analyze whether the lifestyle intervention has a positive effect on quality of life, perceived stress, optimistic outlook on life, breast cancer incidence, and mortality. The study design is outlined in Fig. 1 and includes six visits (SE: study entry, V0: start of intervention, V1: 3 months after start of intervention, V2: 12 months after start of intervention, V3: 24 months after start of intervention, and V4: 36 months after start of intervention). The Standard Protocol Items: Recommendations for Interventional Trials (SPIRIT) checklist and flow diagram are available as Additional files 1 and 2.

**Fig. 1 Fig1:**
[figure not shown]
Design of the trial

### Participants

The goal is to recruit a minimum of 600 patients. Recruitment and study conduct take place at 18 centers of the German Consortium for Hereditary Breast and Ovarian Cancer (GC-HBOC). Table 1 details the study’s inclusion and exclusion criteria.

**Table 1 Tab1:** Study population: inclusion and exclusion criteria

Inclusion criteria (all criteria must apply): • Women with a *BRCA1* or *BRCA2* germline mutation • Age over 18 years • Written informed consent
Exclusion criteria: • Ongoing chemo- or radiation therapy (recruitment is possible 6 weeks after completing therapy) • Metastatic tumor disease • Expectancy of life <3 years • Limited cardiovascular and lung diseases (unstable CHC, heart failure stage IV, chronic obstructive pulmonary disease GOLD IV, maximal blood pressure at rest >160/100 mmHg) • Significant orthopedic problems not allowing exercise • Serious diseases not allowing a participation in group interventions (e.g., psychiatric or internal ailment) • Karnofsky index <60 % • Women with an exercise capacity <50 watts • Food allergies not allowing consumption of a Mediterranean dietary pattern • Vegans • BMI <15 kg/m^2^ • Pregnancy • Insufficient knowledge of the German language • Lack of compliance • Current participation in other lifestyle intervention trials

*CHC* Coronary Heart Condition

### Intervention group

A lifestyle intervention program lasting 12 months is adopted in the intervention group. The program is applied intensively during the first 3 months and is maintained and monitored for the following 9 months through monthly contacts and meetings. The lifestyle intervention program comprises the measures described in the following paragraphs.

#### Physical activity

The LIBRE training program is primarily endurance-oriented training, which is completed during the course of one year. After a mandatory introductory lecture on the theory behind the intervention training, the goal is to increase physical activity to ≥18 MET-h/week (MET = Metabolic Equivalent of Task). This activity level has been correlated consistently with a reduction of morbidity and mortality in patients with breast cancer [8, 19]. This goal should be achieved within the first 12 weeks and maintained throughout the whole study period. Each subject receives an individual training plan, which is continuously adapted according to her fitness status to support this goal. The training is divided into two phases: the intensity of the first phase should be at least 50–60 % of peak oxygen consumption (VO_2_ peak) (initial phase, weeks 1–6), and that of the second phase should be 60–75 % of the VO_2_ peak (optimization phase, weeks 7–12). In the first 12 weeks of the intervention program, training takes place 2 times per week as supervised training and once per week as home-based training (HBT). Afterwards supervised training units are only carried out monthly so that training in phase II (months 4–12) is mainly HBT. Training continues to take place with an intensity of at least 60–75 % of the VO_2_ peak in accordance with the individual training plan.

A record of compliance with the training intervention program as well as with the achieved MET-hours/week is kept in the training diaries (questionnaire on physical activity, V0–V2). Participants are asked to record their daily activities as well as intentional physical activity including intensity and duration of training. The training intensity levels are assessed from spiroergometry and are outlined in the diary, which facilitates training control. Monthly supervised training units (as of V1) offer the opportunity to realign training intensity and discuss any problems with adherence to training. In addition, physical activity is recorded by questionnaires (International Physical Activity Questionnaire, IPAQ) [21, 22] from SE–V4, and physical fitness is assessed by cardiopulmonary exercise testing by spiroergometry (VO_2_ peak) [23] at time points SE, V1, and V2.

#### Nutrition

Within the framework of the LIBRE study, the nutrition intervention is based on the principles of a Mediterranean dietary pattern (MD). Furthermore, obese patients (BMI ≥30 kg/m^2^) are instructed to limit their energy (kilocalorie) intake. Nutrition intervention in the intervention group begins with an intensive 3-month nutrition program during which biweekly nutrition courses led by dietitians take place in groups. The group course includes a cooking class and a guided tour of a supermarket. At the end of the first 3 months, the nutrition courses take place at monthly intervals for the remaining course of the first study year. The main objective of the nutrition intervention is to provide practical nutritional training, which should enable the subjects to achieve a long-term change in their eating habits, replacing former eating habits with the MD. Eating habits are recorded using validated questionnaires (the European Prospective Investigation into Cancer and Nutrition Food Frequency Questionnaire [EPIC-FFQ] and Mediterranean Diet Adherence Screener [MEDAS]) at the time points SE, V1, V2, V3, and V4. Participants of the intervention group additionally received the MEDAS questionnaire at time points V1-6 and V1-9.

#### Psychological support

Psychological support of the intervention group comprises solely an explanation of the psychological data survey questionnaires given to the study participants. Explicit psychological support is not planned. The participants are informed that the objective of the lifestyle study is, among other things, that the lifestyle change including regular physical activity and healthy eating should lead to an improvement in general quality of life, stress reduction, a more optimistic outlook on life, and a better attitude towards endurance training and MD. In order to verify this, the participants receive the questionnaires Trier Inventory for Chronic Stress (TICS), Life Orientation Test-Revised (LOT-R), European Organisation for Research and Treatment of Cancer Quality of Life Questionnaires-Core 30 and BR23 (EORTC QLQ-C30/-BR23), and Evaluation of Physical Activity and Nutrition (“Bewertung koerperlicher Aktivitaet und Ernaehrung” [BKAE]) at different time points (SE, V1, V2, V3, and V4). Advice on psycho-oncological aspects of the LIBRE study is given during the introductory lecture at the beginning of the study. Particular importance is attached to participants giving as detailed information as possible in the survey questionnaires.

Psychological advice given to the study participants should serve to inform the subjects of the significance and improvement of psycho-social lifestyles for the prevention of breast and ovarian cancer, as well as to promote compliance and recognize possible psychological impediments for participation in the study.

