### Control group

The control group will receive a mandatory introductory lecture on the positive effects of physical activity on the incidence and prognosis of breast cancer. Afterwards all participants will be given a brochure providing the most important facts on this topic.

Contrary to the intervention group, no training and no physical activity diaries will be provided. Changes in physical activity behavior are measured identically to the interventional group through questionnaires (IPAQ at SE–V4) and examinations of physical capacity (VO_2_ peak) at time points SE, V1, and V2.

Additionally, a dietitian-led nutrition group lesson on healthy eating will be held for the control group. During this lesson the subjects receive general information based on the recommendations of the German Society of Nutrition, which is referred to as “usual care in Germany” in this study. Eating habits will be recorded identically as in the intervention group via validated questionnaires (EPIC-FFQ and MEDAS) at the defined time points SE, V1, V2, V3, and V4.

The psychological guidance of the control group consists of an explanation of the psychological data entry forms which are given to the study participants. An explicit psycho-oncological intervention strategy is also not intended in this group. The participants will be informed that changes in daily routine concerning physical activity and dietary habits among other things should resolve in improvement of quality of life, a reduction of stress, and a more optimistic approach to the future. In order to verify this, the participants will receive questionnaires (TICS, LOT-R, EORTC QLQ-C30/-BR23, and BKAE for registration of changes in attitude towards physical activity and MD) at SE and V1–V4. The psychological information of the control group corresponds to that of the intervention group.

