A limitation of the trial might occur during randomization, especially for highly motivated participants. They may be disappointed if randomized to the control arm, and therefore may withdraw from the study or exercise nonetheless. In addition, cross-over communication regarding the Mediterranean dietary pattern between the intervention and control group cannot be completely avoided. On the other hand, it might be difficult for less motivated working women or mothers to integrate the exercise program into their everyday life.

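### The questionnaire explanation tells both arms which way quality of life, stress and optimism should move, an avoidable added risk of expectancy bias in open-label self-reports

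*Protocol article*

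**What the plan says.** All references are to the protocol article.

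- **Psychological support (intervention group).** This support "comprises solely an explanation of the psychological data survey questionnaires given to the study participants". The section then reports what participants are told: one objective of the study, among others, is that the lifestyle change "should lead to an improvement in general quality of life, stress reduction, a more optimistic outlook on life, and a better attitude towards endurance training" (the Mediterranean diet is named as well). The following sentence begins "In order to verify this, the participants receive the questionnaires Trier Inventory for Chronic Stress (TICS" and goes on to list LOT-R, EORTC QLQ-C30/-BR23 and BKAE.
- **Control group.** Psychological guidance is again an explanation of the forms. Women are told that changes in activity and diet "should resolve in improvement of quality of life, a reduction of stress, and a more optimistic approach to the future", and receive the same instruments for the same stated purpose. The section closes: "The psychological information of the control group corresponds to that of the intervention group".
- **What each arm receives.** The intervention group has a 12-month training and nutrition program. The control group has an introductory lecture, a brochure and one dietitian-led group lesson, with no training.
- **Study endpoints and Table 3.** Quality of life, stress and optimism are secondary endpoints. BKAE is listed among the other outcomes.
- **Discussion.** Of highly motivated participants it says: "They may be disappointed if randomized to the control arm".

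**The concern.** A respondent who has been told which answer the study hopes for may shift her answers toward it, whether or not her state has changed. The usual protections against this are blinding, an objective measurement, or neutral presentation of the instrument. Blinding is not possible with a training and diet program, and these outcomes are self-reported, so only neutral presentation is left. As described, the briefing gives it up by stating the expected direction alongside the forms that test it.

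At stake is how a difference between arms on TICS, LOT-R, EORTC QLQ-C30/-BR23 and BKAE can be read. The Background section places quality of life, optimism and perceived stress in its statement of aims, and the Measurements section states a hypothesis of improvement for each. If part of a difference is a reporting shift, the effect of exercise and diet on these outcomes is overstated.

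**Working it through.** **1. Is the direction stated, and where?** The intervention section says the support consists only of the questionnaire explanation and then gives the directional message, so the message belongs to that explanation. The control section has the same order: explanation of forms, directional message, instruments. The article summarises the briefing and does not reproduce the script; this reading rests on that summary.

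**2. Is the message the same in both arms?** Largely.

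| | Intervention | Control |
|---|---|---|
| Quality of life, stress, optimism expected to improve | yes | yes |
| Attitude to training and diet expected to improve | yes | not stated, though BKAE is given |
| Worded as a study objective | yes | no |
| Instruments given to verify it | yes | yes |
| Structured program delivered | yes | no |

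**3. Does equal wording cancel the effect?** Not necessarily. The message credits benefit to a lifestyle change. A woman in the intervention arm can apply it to what she is receiving. A woman in the control arm hears it without a structured program. The last row of the table is where the arms differ, and participants can see it.

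**4. Which outcomes are exposed?** TICS, LOT-R and EORTC QLQ-C30/-BR23 (secondary) and BKAE (other). BMI and VT1 are measured, not reported, and are not affected by this route. MEDAS is self-reported, but adherence is not among the outcomes named in the message.

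**5. How large could it be?** The article gives no figure from which a bias can be derived. The following is an illustration under assumptions.

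- Per arm: 490 evaluable / 2 = 245 (section on sample size). That count belongs to the co-primary endpoints; applying it to the questionnaires is an assumption.
- Standard error of a standardised mean difference: sqrt(2/245) = 0.090.
- Assumed: no true effect, two-sided alpha 0.05, between-arm reporting shift b in SD units.
- Probability of a significant result favoring the intervention: Φ(b/SE − 1.96).

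| Assumed shift b (SD) | b/SE | Probability |
|---|---|---|
| 0 | 0 | 2.5 % |
| 0.05 | 0.55 | about 8 % |
| 0.10 | 1.11 | about 20 % |
| 0.15 | 1.66 | about 38 % |
| 0.20 | 2.21 | about 60 % |
| 0.30 | 3.32 | about 91 % |

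The table shows how sensitive a trial of this size is to any between-arm reporting shift. It does not say how much of such a shift comes from the briefing. Open allocation, consent and a year of coaching would produce some of it anyway; only the increment due to the wording can be avoided, and that may be near zero.

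**The case against.** The strongest reply has four parts.

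- **This is disclosure of an objective, and the briefing is already matched.** In the intervention section the message is worded as an objective, and in both sections the questionnaires follow as its test. Nobody is told how to answer. This stands as far as intent goes. It does not remove the risk, because the respondent still learns the hoped-for direction together with the form, and matched words meet unmatched programs.
- **The direction of bias is not shown.** This stands in part. A reader might infer that the article expects control women to score worse out of disappointment. It does not say so. The Discussion says only that some, especially the highly motivated, may be disappointed; it ties this to randomization and names withdrawal or exercising anyway as the consequences. Exercising anyway would shrink the contrast. The message could also raise expectations among controls.
- **The design has some protection.** Baseline is measured at study entry, BKAE contains reverse-scaled items, and LOT-R is described as measuring a personality variable. These help a little. Reverse scaling guards against agreeing with every item, not against a respondent who knows the hypothesis. It does show that the trial takes conforming answers seriously.
- **The psychological advice has a purpose.** The article says it should support compliance. This stands, and limits the fix. A reader might infer that the introductory lecture also announces these directions and should be stripped of them. The article says that psycho-oncological advice is given there, but not that the lecture states a direction for quality of life, stress or optimism.

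**Conclusion.** The point holds as an avoidable added risk of bias, not as a demonstrated bias. The explanation of the questionnaires states the expected direction in both arms, allocation is open, and only one arm receives the program credited with the benefit. The self-reported psychological secondary endpoints and BKAE are therefore exposed to expectancy or demand effects. Apparent benefit is the more likely direction, by reasoning and not by evidence in the document.

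The size is unknown. The 20 % to 60 % range for a spurious significant benefit rests wholly on an assumed shift of 0.10 to 0.20 SD, 245 women per arm and alpha 0.05, and it is not attributable to the wording alone.

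Two stronger conclusions might be drawn, and the document supports neither. One is that every psychological endpoint is pushed toward false benefit at every visit from V1 to V4; nothing establishes a uniform direction, least of all at 24 and 36 months, after the 12-month program has ended. The other is that a positive difference could not be read as an effect of exercise and diet at all; it would need caution, as any open-label self-report does. The co-primary results on BMI and VT1 are untouched by this route. This is an inexpensive improvement to secondary outcomes, not a flaw in the trial's main comparison.

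**What to change.** Replace the directional statement in the questionnaire explanation of both arms with one neutral script. For example: the study asks about well-being, stress and outlook on life; there are no right or wrong answers; it is not known whether the groups will differ. Keep the request for detailed answers. Leave the motivational content on exercise and diet in the lecture and courses as it is, since it serves compliance. Record the date of the change at each center, because the Trial status section says recruitment is under way.

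The cost is rewording one briefing text and informing the 18 centers; no new data, staff or participants are needed. The drawbacks are that women briefed before and after the change will have heard different explanations, and that the risk is reduced but not removed, because allocation stays open and consent discloses the study purpose.
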